## Objectives

### Primary objective

The primary purpose of this study is translation and cultural adaptation of the school-based mental health literacy program guide as well as validation of the *Guide Cymru* program in Iranian adolescent students aged 13–15. Also, the study deals with with the implementation and evaluation of program.

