### Population and sampling

The study population includes all adolescents in grade 8th and 9th year of secondary schools (13 to 15 years old) using stratified random sampling from Sirjan city; a city in Kerman province in the southeast of Iran. Using the effect size and primary data of Nguyen, Dang [17] study and considering the first type error at the level of 0.05 and the power of 0.80, the sample size was calculated to be 281 students in each of the intervention and control groups. Finally, 562 students of the first secondary schools of Sirjan city will be included in the study.$${n}_{1}={n}_{2}=\frac{\left({S}_{1}^{2}+{S}_{2}^{2}\right){\left({Z}_{1-\frac{a}{2}}+{Z}_{1-\beta }\right)}^{2}}{{\left(\overline{{X }_{1}-\overline{{X }_{2}}}\right)}^{2}}$$

After receiving the list of first secondary schools from the Department of Education, in order to prevent the effect of the intervention and based on the three geographic regions of Sirjan, a total of 20 first secondary schools will be randomly divided into two groups of control and intervention. This number of schools was determined based on the assumption that each school has a minimum of 28 students to be included in the study. According to the procedure for implementing the intervention, two teachers (a health coach and an educational coach) will be chosen from each school. Twenty teachers from each of the two groups (intervention and control) will take part in the study, for a total of 40 teachers. If a teacher expresses unwillingness, will be replaced by another teacher.

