### Step 3: Application of an educational program for students based on the Guide Cymru

Prior to the start of study, written consent will be obtained students' parents. Teachers will provide informed consent forms to parents. To keep the confidentiality and anonymity, consent forms will be gathered, and the study team will develop an identification code for each student, which will be completed by teachers. It is worth mentioning that this code will be will be used in student evaluation. Participants are also assured that their personal information will be kept strictly confidential. The evaluation is based on three questionnaires measuring mental health literacy, general knowledge of mental health, and attitudes toward mental disorders, allowing the teacher to assess the significant dimensions of mental health literacy. Before teaching the guide in the classroom, the pre-test will be administered; following the completion of the sixth module, the post-test will be administered again; and two months later, the questionnaires will be administered once more. Students will attend sessions on the specified day and time depending on the allocated groupings. Following the pre-test, a qualified teacher will lead an educational content session of the school-based mental health literacy program based on the six modules under the supervision of the researcher and psychologist. The Guide training consists of six modules taught sequentially over the course of eight to ten sessions. The modules are constructed in such a manner that each one is conducted in 60-min lessons. Among all modules of the Guide, the third module is the longest and most informative module, requiring more teaching time than the others. As a result, three 50-min intervals will be allotted to this module. In the control group, the general content of the Guide Cymru educational program will be presented by a psychological expert with the coordination of teachers and students. Finally, after the evaluation of the school-based mental health literacy program, teachers and pupils in the control group will receive the Guide Cymru program guide.

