### Phase 4) Evaluation of the impact of Guide Cymru's school-based mental health literacy program

According to study of improvements in students’ mental health literacy with use of a mental health curriculum in Canadian schools [13], mental health literacy, general knowledge of mental health and attitudes related to mental disorders of students and teachers before and after the implementation of the educational intervention and with a 2-month follow-up were evaluated and the results will be compared before, immediately after, and two months after the educational intervention. By comparing a student's pre-test, post-test, and two-month post-test scores, this method of evaluation enables a precise determination of student's learning.

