### Data analysis

To describe and analyze data, descriptive and inferential statistical methods are utilized. Qualitative variables will be presented as frequency and percentage, while quantitative variables will be presented as mean and standard deviation. The paired t-test will be used to measure the significant difference in mental health literacy, knowledge, and attitude between the before and after surveys. *p* < 0.05 will be considered as a significant level. SPSS software (version 26) will be used for analysis.

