### Strengths and limitations

One of the study's strength is that the Guide will be localized, thereby enabling the substitution of educational content that conflicts with Iranian culture with more suitable material. Another strength is that the educational content of the mental health literacy program will be delivered by school instructors, and its efficacy will align more closely with the program's objectives. From other strengths, this study is a randomized controlled trial with an intervention and a control group, and also the most important point in this study will be the measuring tool of the MHLS questionnaire, which includes all the key components of mental health literacy.

This study also has limitations. The absence of the school-based mental health literacy program guide in the students' curriculum is one of the limitations of this study. Therefore, instructors and students may lack the cooperation necessary for the program's implementation.

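### Three student outcomes share one 0.05 threshold with no primary outcome or time point named, and the stated two-survey test cannot deliver the three-survey comparison promised elsewhere in the protocol

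*Protocol article*

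**What the plan says.** All references are to the protocol article.

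- **Data analysis** gives one inferential procedure: "The paired t-test will be used to measure the significant difference in mental health literacy, knowledge, and attitude between the before and after surveys". The threshold follows: "0.05 will be considered as a significant level". The three outcomes are not ranked.
- **Primary objective** opens: "The primary purpose of this study is translation and cultural adaptation of the school-based mental health literacy program guide". It goes on to validation and then adds that the programme will be implemented and evaluated. It attaches no scale and no time point to that evaluation.
- **Population and sampling** sets the size "considering the first type error at the level of 0.05 and the power of 0.80", giving 281 per group and 562 in total. The effect size comes from a cited earlier study. The outcome it belongs to is not named.
- **Step 3** of Phase II has students answer the questionnaires before teaching and after the sixth module, "and two months later, the questionnaires will be administered once more".
- **Phase 4** (evaluation of impact) states that "the results will be compared before, immediately after, and two months after the educational intervention". It applies this to students and teachers.
- **Strengths and limitations** comes nearest to a ranking: "the most important point in this study will be the measuring tool of the MHLS questionnaire". This describes the MHLS as an instrument and does not designate it as the endpoint.

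**The concern.** There are two faults, and they are distinct.

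First, three outcomes stand on an equal footing at the same threshold. The 0.05 error rate and the 80% power in the sample-size paragraph should belong to one identified comparison. Here they belong to none. A reader of the results could not tell whether the headline scale was chosen before or after the data were seen.

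Second, a paired t-test between two surveys cannot produce the three-survey comparison described under Phase 4. If the plan is followed as written, the two-month survey is collected but has no stated analysis, and that survey is the one that shows whether gains last.

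The two faults combine: the decisive scale is open, and so is the decisive time. This matters because the Practical objective section expects the Guide to serve as a national protocol for the school curriculum.

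**Working it through.** **1. The plan's own figure.** The protocol's formula is n per group = (S1² + S2²)(z₁₋α/₂ + z₁₋β)² / (difference in means)². The means and SDs are not given, so 281 cannot be reproduced forwards. Assuming equal SDs and solving backwards with z values 1.960 and 0.842:

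- d = √[2 × (1.960 + 0.842)² / 281] ≈ 0.236 SD.
- Putting 0.236 back in returns 281 per group and power 0.80.

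So 281 corresponds to a standardised difference of about 0.236 on some scale. The document does not say which.

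**2. Number of stated tests.** Data analysis gives three outcomes and one before-after comparison, which makes 3 student tests. This assumes one test per outcome; the text does not say whether the arms are tested separately.

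**3. Chance of at least one p < 0.05 when nothing has changed.** If independent: 1 − 0.95³ = 1 − 0.857 = 0.143.

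The scales are completed by the same students, so correlation is likely. The documents give no value. Simulating three equicorrelated normal statistics, two-sided at 0.05, gives:

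| Assumed correlation | Chance of at least one |
|---|---|
| 0 | 14.3% |
| 0.3 | 13.6% |
| 0.5 | 12.5% |
| 0.7 | 10.9% |
| 0.9 | 8.3% |
| 1.0 | 5.0% |

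**4. If the two-month survey were tested separately in the same way.** 3 outcomes × 2 post-baseline times = 6 tests, and 1 − 0.95⁶ = 0.265 if independent. At correlations of 0.3, 0.5 and 0.7 the figure is about 24%, 21% and 16%. This is conditional, since no such tests are stated.

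**5. What naming one primary outcome saves.** With one primary outcome, alpha stays at 0.05 and multiplicity requires no increase on 281. With three co-equal outcomes under Bonferroni, alpha is 0.05/3 = 0.0167 each. A difference of 0.236 SD then needs 375 per group (750 in total). Keeping 281 would cut power per outcome from 80% to 65.8%. These figures are illustrative: they rest on the back-solved effect and, like the protocol's formula, take no account of schools.

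**6. The two statements on timing, side by side.** Phase 4 compares three surveys: before, immediately after and two months after. Data analysis tests a difference between two. No other inferential method is named, so the passages must be reconciled.

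**The case against.** The strongest objection is that this is a journal article and that the analysis plan and full protocol are not shown. Multiplicity adjustment, the labelling of secondary outcomes and details of a repeated-measures model are commonly left to those documents. That stands, and the point does not rest on their absence. It rests on two things in the printed text. The article sets out objectives, a sample size and an analysis without tying the sample size to any outcome. And its stated test does not match its stated comparison.

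Several stronger readings are tempting, and the document does not support them:

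- **A false-positive rate of 26.5%.** This needs six tests. Data analysis states three, and the two-month survey has no stated test at all, so 26.5% is a ceiling for a plan that is not written down.
- **Any one significant result counts as success.** No success rule appears. The text merely does not prevent that use.
- **The primary objective excludes effectiveness.** It does not; it includes evaluation. What is missing is a measure and a time point.
- **The MHLS is already primary, or the 281 is an MHLS figure.** The MHLS is praised as a tool. The source scale of the 281 is not named, so it cannot simply be relabelled.
- **14.3% is the chance of falsely claiming that the programme works.** A paired before-after test measures change over time, not a difference between randomised arms. It could reject because of retesting or maturation. The 14.3% describes multiplicity only.

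It is also fair to say that the choice of scale and time is open to argument. The abstract frames the aim around stigma and help-seeking, and nothing in the text favours two months over the immediate post-test.

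**Conclusion.** The concern holds in limited form. The plan applies 0.05 to three unranked student outcomes, names no primary effectiveness outcome or time point, and sizes the trial on an unidentified scale. The false-positive chance for the three stated tests is at most 14.3%, and about 11% to 14% for correlations of 0.7 to 0.3. It would be lower still if the scales were more strongly correlated. These figures assume one test per outcome, no true change, and correlations that the documents do not give. Teacher outcomes would add further tests.

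The mismatch between the Phase 4 section and the Data analysis section needs no assumption: a two-survey test cannot deliver a three-survey comparison. The change should be made. It is inexpensive, and it settles what the 0.05 and the 80% power refer to.

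**What to change.** 1. Before the outcome data are analysed, name one primary student outcome and one time point, tested as a between-arm difference at 0.05. The MHLS total is a natural candidate given the remark under Strengths and limitations. The choice of scale and time is the investigators' to make.
2. Make the other scales, the other time point and the teacher outcomes secondary, with Holm adjustment or labelled exploratory.
3. Replace the paired t-test with one repeated-measures model that includes both post-baseline surveys, adjusts for baseline, compares the arms and accounts for the 20 randomised schools. This also reconciles Data analysis with Phase 4.
4. State which scale the 281 per group was derived from. If it is not the primary outcome, restate the power for the primary outcome.

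Cost: items 1 to 3 change wording and analysis but add no data collection. Item 4 may need a fresh calculation, and the restated power may be less favourable. The remaining scales and the other time point can no longer carry the headline claim alone.

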## Discussion

The use of a curriculum-integrated mental health literacy resource (guide) offered by classroom instructors may aid students in understanding mental health and mental illness, eventually resulting in a decrease in the stigma of mental illness and an increase in the number of people seeking treatment. Additionally, it will encourage the development of mental health literacy in teachers and students by improving teachers' and students' attitudes about mental health.

### Strengths and limitations

One of the study's strength is that the Guide will be localized, thereby enabling the substitution of educational content that conflicts with Iranian culture with more suitable material. Another strength is that the educational content of the mental health literacy program will be delivered by school instructors, and its efficacy will align more closely with the program's objectives. From other strengths, this study is a randomized controlled trial with an intervention and a control group, and also the most important point in this study will be the measuring tool of the MHLS questionnaire, which includes all the key components of mental health literacy.

This study also has limitations. The absence of the school-based mental health literacy program guide in the students' curriculum is one of the limitations of this study. Therefore, instructors and students may lack the cooperation necessary for the program's implementation.

## Data Availability

The datasets generated and/or analyzed during the current study are available from the corresponding author on reasonable request.

## Abbreviations

CVI: Content Validity Index
CVR: Content Validity Ratio
SAM: Suitability Assessment of Materials
RAM: Readability Assessment of Materials
MHL_S_: Mental Health Literacy Scale
